# Pregnancy-associated progression of chronic kidney disease: a study protocol for the development and validation of a clinical predictive tool (PREDICT)

**DOI:** 10.1007/s40620-023-01788-5

**Published:** 2023-11-21

Women with chronic kidney disease (CKD) in reproductive years may frequently wish to consider the option of pregnancy. It is estimated that early-stage CKD is present in 3:100 pregnancies, and later stage CKD affects 1:750 pregnancies [1]. Chronic kidney disease is associated with an increased risk of maternal and neonatal adverse outcomes which are inversely related to deteriorating kidney function and include pre-eclampsia, small-for-gestational-age infants, preterm birth, and accelerated decline in kidney function postpartum [2]. There is no reliable contemporaneous prediction tool for pregnancy and kidney outcomes for women with CKD, despite requests from women with CKD and their health care professionals to provide more resources and support [2]. This study aims to develop and validate two prediction models that estimate (i) the likelihood of a ≥ 25% reduction in estimated glomerular filtration rate (eGFR) or initiation of renal replacement therapy between 6 weeks and 12 months postpartum and (ii) the likelihood of a small-for-gestational-age (SGA < 3rd percentile) infant and/or premature birth < 34 weeks’ gestation.

The models will be developed and validated using seven international datasets. Model development will use the National Registry of Rare Kidney Diseases (RaDaR) from the UK Renal Registry (UKRR), a United Kingdom (UK) wide, linked dataset between RaDaR, UKRR, Hospital Episode Statistics (HES) and Maternity Services Data Set (MSDS). This cohort includes any woman with a diagnosis of kidney disease in the UK with maternity records from 1997 onwards, including those with ICD-10 codes for CKD in Hospital Episode Statistics, consented to participate in RaDaR or with data reported to UKRR.

External validation will be performed in the following datasets:i.West and East Kent integrated maternal and laboratory data from the University of Kent. This includes routinely collected data from hospitals in Kent (UK).ii.Stockholm Creatinine Measurement (SCREAM). This is an observational dataset with laboratory data of individuals residing or accessing healthcare in the region of Stockholm (Sweden) with results. SCREAM has previously been described in detail [3]iii.The Ontario Renal Network Pregnancy Cohort. This is a population-based cohort of women in the province of Ontario (Canada) with a baby born between 2007 and 2020. Administrative health databases linked using unique identifiers at Institute for Clinical Evaluative Sciences (ICES) are used to capture all hospital births in Ontario and outpatient laboratory testing.iv.Cohort data from three obstetric studies within the UK collected between 2010 and 2018. These studies have previously been described in detail [2, 4, 5].

The model development and validation will follow the Transparent Reporting of a multivariable prediction model for Individual Prognosis Or Diagnosis statement recommendations (TRIPOD) [6]. Ethical approval was given by the Health Research Authority (London Bloomsbury Research Ethics Committee, Ref: 23/LO/0258). The study is registered on ClinicalTrials.gov (Ref: NCT05793346).

Women with an eGFR less than 90 ml/min/1.73 m^2^ using the Chronic Kidney Disease Epidemiology Collaboration (CKD-EPI 2009) [7] without ethnicity adjustment within 24 months prior to conception will be included. Women established on dialysis at time of conception, multi-fetal pregnancies, known inpatient eGFR measurement and those with no preconception eGFR within 24 months will be excluded.

Candidate model predictors are based on previous studies reporting risk factors for pregnancy and kidney outcomes in women with CKD and availability within the cohorts (Table 1). All predictors are within routine care for women with CKD in pregnancy enabling the acceptability of implementation and generalisability of the models.

**Table 1 Tab1:** Candidate predictors for model development

Candidate predictor	Definition	Measurement unit
Maternal age	Age at conception	Years
Maternal ethnicity	Self-reported ethnicity. This, if possible is categorised into four groups following published guidance from UK government	Asian, Black, Caribbean or African, mixed or multiple ethnic groups, White and other
Maternal BMI	Maternal body mass index (BMI) at first pregnancy visit	kg/m^2^
Multiparous	Prior record of delivery after 24 weeks’ irrespective of outcome	Yes or no
Chronic hypertension	Antihypertensive medications before pregnancy or before 20 weeks’ gestation/or systolic blood pressure > 140 mmHg or diastolic blood pressure > 90 mmHg before 20 weeks’ gestation, or ICD 10 code for hypertension, or two physician claims for hypertension within two years prior to pregnancy	Yes or no
Aetiology of CKD during pregnancy	Primary cause of CKD categorised into eight pre-defined categories. (1) glomerulonephritis (excluding systemic lupus erythematosus), (2) chronic Pyelonephritis or Vesicoureteral reflux, (3) autosomal dominant polycystic kidney disease (ADPKD), (4) diabetic nephropathy (not including women with other CKD cause and co-existing diabetes), (5) congenital or inherited (other than ADPKD), (6) kidney transplant, (7) systemic lupus erythematosus, (8) other	
Pre pregnancy eGFR	eGFR within 24 months of conception calculated using CKD-EPI equation without ethnicity adjustment	ml/min/1.73 m^2^
Pre pregnancy proteinuria	uPCR, uACR or urine dipstick within 24 months of conception	Normal (uACR < 3 or uPCR < 15 mg/mmol, urine dipstick normal) moderate (uACR 3–30, uPCR 15–50 mg/mmol, or urine dipstick 1 +). severe (uACR > 30, uPCR > 50 mg/mmol or urine dipstick 2 +)

*CKD* chronic kidney disease, *CKD-EPI* Chronic Kidney Disease Epidemiology Collaboration 2009, *eGFR* estimated glomerular filtration rate, *ICD* International Classification of Diseases, *uACR* urine albumin-to-creatinine ratio, *uPCR* urine protein-to-creatinine ratio

There are two binary outcome measures. Firstly, a ≥ 25% reduction in eGFR or initiation of renal replacement therapy between 6 weeks and 12 months postpartum. This timeframe is applied as typically, serum creatinine levels may peak within the first few weeks postpartum but return to pre-pregnancy concentrations [8]. This outcome was chosen from surveys including 90 women with CKD and 73 healthcare professionals. The second outcome is a composite outcome of preterm birth defined as less than 34 weeks’ gestation and/or SGA < 3rd percentile (INTERGROW).

This is a secondary analysis on pre-existing data and therefore the sample size is fixed; however using *pmpsampsize* package, a sample size of at least 494 pregnancies is estimated to be adequate to avoid overfitting [9]. Characteristics of the cohort for model development and validation will be described, including missing data. Listwise deletion will be applied for model development. A sensitivity analysis will be performed using multiple imputation.

The development of both models will follow the same analyses as both outcomes are dichotomous. Initial univariable logistic regression models will be performed on each candidate predictor to initially assess their crude association with the outcome and we will fit a multivariable model containing all predictors. Then backwards elimination will be used to successively remove the least significant predictors in the model using the Akaike’s Information Criterion and significance. A liberal *p* value of 0.10 will be applied for retention. We will also consider predictors based on clinical knowledge and previous research findings. Variance inflation factor will be performed prior to fitting the final model to identify any collinearity between the predictor variables. The final predictors will be included in a multivariable logistic regression model. The final models will be assessed for overall performance (model fit), calibration and discrimination. Clinical performance will be assessed through positive predictive value, negative predictive value, sensitivity and specificity.

Final models will be subject to internal and external validation to assess performance of the models. Internal validation using bootstrapping will enable us to examine for potential overfitting of the developed models. We will externally validate the final models in the international cohorts. The overall predictive performance, clinical performance, discrimination and calibration will be evaluated in each cohort.

The purpose of this study is to develop and validate two prediction models estimating the likelihood of: (i) having a 25% or greater decline in kidney function or initiation of renal replacement therapy, and (ii) having a delivery before 34 weeks or a SGA infant. The provision of these models will help to facilitate informed decision-making amongst women and their partners. The provision of risk information will support clinicians in providing personalised maternity counselling and care.

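### The record that admits a woman to the development cohort need not predate the kidney outcome, so some women can enter because they had it

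*Protocol article*

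**What the plan says.** The article has no numbered sections, so places are given by content.

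- **Development data (opening section).** The frame is any woman with a kidney diagnosis and a maternity record: "This cohort includes any woman with a diagnosis of kidney disease in the UK with maternity records from 1997 onwards". The routes in are listed as "including those with ICD-10 codes for CKD in Hospital Episode Statistics, consented to participate in RaDaR or with data reported to UKRR". No order in time is set between the diagnosis, code, consent or report and the pregnancy.
- **Eligibility.** Women qualify on an eGFR below 90 by CKD-EPI 2009, "without ethnicity adjustment within 24 months prior to conception will be included". The list of exclusions begins "Women established on dialysis at time of conception, multi-fetal pregnancies, known inpatient eGFR measurement"; its last item is a missing eGFR for the two years before pregnancy. The eGFR and dialysis status are tied to conception. Nothing concerns the date of the diagnosis or registration.
- **Outcome (i).** It is "a ≥ 25% reduction in eGFR or initiation of renal replacement therapy between 6 weeks and 12 months postpartum".
- **Analysis.** Incomplete records are deleted listwise, with multiple imputation as a sensitivity analysis. Internal validation is by bootstrap, and calibration is assessed in each external cohort. One of these is Ontario: "This is a population-based cohort of women in the province of Ontario (Canada) with a baby born between 2007 and 2020".

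**The concern.** A large fall in eGFR, or the start of renal replacement therapy, is the kind of event that can lead to a CKD code, recruitment to RaDaR or a renal registry report. These are also the routes into the development cohort.

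Take two women with a preconception eGFR of 80 and no kidney record. One loses at least 25% of her eGFR postpartum, is then coded, and enters. The other keeps her function, is never coded, and is absent. Entry then depends partly on the outcome being predicted.

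The effect would be uneven. Women with advanced disease are probably recorded before pregnancy anyway, so their observed risk hardly moves. Women with mild disease are the least certain to have a prior record, so their observed risk can rise. The model would then start from too high a baseline at higher eGFR and show too weak a gradient with eGFR. The article intends the tool for counselling and informed decisions, so the women at stake are those with milder disease. The bootstrap resamples the same selected women and cannot show the problem.

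**Working it through.** **The plan's own figure.** The only related number is the minimum of 494 pregnancies. The article does not give the assumed prevalence, model fit or number of parameters, so 494 can be neither confirmed nor refuted. The point does not depend on it.

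**Inputs.** The entry routes, eligibility rules and outcome come from the article. It gives no figure for when women were first recorded, so every number below is an assumption.

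- r = true outcome risk
- f = share of eligible women already recorded beforehand, taken as the same with and without the event
- q1, q0 = chance of a later first record with and without the event

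**Formula.** A woman with the event is in the cohort with probability f + (1 − f)q1, and one without it with probability f + (1 − f)q0. Hence

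observed odds = true odds × [f + (1 − f)q1] / [f + (1 − f)q0].

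**Illustration A: one risk group, r = 10%, q1 = 0.5.**

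| f | q0 | Odds factor | Observed risk |
|---|---|---|---|
| 0.3 | 0.10 | 0.65/0.37 = 1.76 | 16.3% |
| 0.5 | 0.10 | 0.75/0.55 = 1.36 | 13.2% |
| 0.8 | 0.10 | 0.90/0.82 = 1.10 | 10.9% |
| 0.3 | 0.25 | 0.65/0.475 = 1.37 | 13.2% |
| 0.5 | 0.25 | 0.75/0.625 = 1.20 | 11.8% |
| 0.8 | 0.25 | 0.90/0.85 = 1.06 | 10.5% |

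If q1 = q0, or if f = 1, the factor is 1.00 and there is no bias. If later records are not admitted at all, the factor is f/f = 1.00.

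**Illustration B: mild against severe disease.**

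- Mild (eGFR 60–89), r = 8%, f = 0.3, q1 = 0.7, q0 = 0.2. With the event: 0.08 × (0.3 + 0.7 × 0.7) = 0.0632. All entrants: 0.3 + 0.7 × (0.08 × 0.7 + 0.92 × 0.2) = 0.468. Observed risk 0.0632/0.468 = 13.5%.
- Mild, lighter assumptions (f = 0.5, q1 = 0.5, q0 = 0.3): 0.060/0.658 = 9.1%.
- Mild, heavier assumptions (f = 0.2, q1 = 0.8, q0 = 0.15): 0.0672/0.3616 = 18.6%.
- Severe, r = 35%, f = 0.97, q1 = 0.99, q0 = 0.9: 0.3499/0.9979 = 35.1%.

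The true severe-versus-mild odds ratio is (0.35/0.65)/(0.08/0.92) = 6.19. The observed ratio is 3.46 under the main assumptions, 5.38 under the lighter and 2.37 under the heavier.

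In B the odds factor for mild disease is 0.79/0.44 = 1.80, with 0.75/0.65 = 1.15 under the lighter and 0.84/0.32 = 2.63 under the heavier assumptions. Two of the three lie above the range in A because B assumes later recording that is more sensitive to the event. B shows the shape of the distortion and is not an estimate of its size.

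**The case against.** The article condenses a fuller protocol that may contain a record-date rule, and the sentence on the development data can be read as describing what the linkage holds. That limits confidence. It does not dispose of the point, because the article gives both the source frame and the eligibility criteria, dates other items with care (eGFR, proteinuria, hypertension), and leaves the qualifying record undated.

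Several features narrow the route:

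- A woman with normal or unmeasured preconception eGFR cannot enter through her outcome.
- Preconception proteinuria is a candidate predictor in Table 1. Under listwise deletion, a woman without a result drops out of the primary analysis. A routine dipstick is enough to keep her in, however, and multiple imputation could bring back women without one.
- Table 1 records the cause of CKD during pregnancy, which shows the intended population. A cause assigned later, or the residual category, could still fill the field.
- The article does not say which linked source supplies eGFR for the development set, so the number of unrecorded women with a qualifying result is unknown.

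External validation also counts for the plan. Ontario is population-based and SCREAM rests on laboratory data, so neither is described as entered by diagnosis, and calibration there could expose an inflated baseline. It would not correct it, and the signal would be mixed with differences between countries and health systems.

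A reader might infer that the finished tool will overstate risk in mild disease. The document does not support that, since it gives no recording rates and the bias disappears if later recording is unrelated to the event. A reader might also infer that only records dated before conception are acceptable. That goes too far for outcome (i): a code first made at antenatal care or delivery precedes the outcome window and cannot have been produced by an event within it.

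**Conclusion.** The point stands as a gap in cohort definition that should be fixed. Followed as written, the plan lets a record generated by outcome (i) admit a woman to the data used to model outcome (i). The preconception eGFR rule and deletion for missing proteinuria reduce the route without closing it.

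The direction is upward if later recording is likelier after the event than without it, which is plausible but not documented. The size is unknown. The illustrative odds inflation of about 1.06 to 1.76 rests on f from 0.3 to 0.8, q1 of 0.5 and q0 of 0.1 to 0.25. The fall in the odds ratio from 6.19 to 3.46 rests on stronger assumptions still. Confidence is moderate, because the full protocol may already hold a date rule. If it does, one sentence confirming it would settle the matter.

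**What to change.** Add one eligibility rule: the first qualifying record (CKD code, recorded RaDaR diagnosis or consent, or UKRR report) must predate the outcome (i) window, that is, be dated before 6 weeks postpartum. State which RaDaR date is used. No pregnancy is then admitted on a record that the outcome could have generated.

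Report how many pregnancies were first recorded before conception, during pregnancy and postpartum. Refit both models as a sensitivity analysis restricted to records dated before conception. This also covers recording prompted by decline during pregnancy, or by delivery complications relevant to outcome (ii). Keeping the stricter cutoff as a sensitivity analysis avoids discarding, from the main model, women with true prior CKD who were first coded at an antenatal or delivery admission.

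The work is a date filter on the linked data and one added sentence. The cost is somewhat fewer pregnancies, mainly in mild disease, so the remaining number should be checked against the stated minimum of 494.

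### Four of the six external validation datasets are UK cohorts that may share pregnancies with the UK-wide development cohort, and no listed exclusion separates them

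*Protocol article*

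**What the plan says.** The protocol article's opening section sets the number of sources: "The models will be developed and validated using seven international datasets". The development source is a national linkage of RaDaR, UKRR, Hospital Episode Statistics and maternity data. Its coverage is described as follows: "This cohort includes any woman with a diagnosis of kidney disease in the UK with maternity records from 1997 onwards". The same sentence names the routes of entry: "including those with ICD-10 codes for CKD in Hospital Episode Statistics, consented to participate in RaDaR or with data reported to UKRR". It gives no end date and leaves out no region.

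The list of external validation datasets follows. Item i is Kent: "This includes routinely collected data from hospitals in Kent (UK"). Items ii and iii are SCREAM (Stockholm) and the Ontario cohort. Item iv reads "Cohort data from three obstetric studies within the UK collected between 2010 and 2018".

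The eligibility paragraph includes women with an eGFR below 90 in the 24 months before conception. It excludes women established on dialysis, multi-fetal pregnancies, inpatient eGFR measurements and women with no preconception eGFR. The validation paragraph states: "We will externally validate the final models in the international cohorts". Performance is to be evaluated in each cohort.

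**The concern.** External validation asks how a model performs in people who had no part in estimating it. Here the development population is defined nationally and by diagnosis, while several of the validation datasets are parts of the same country. A woman with diagnosed kidney disease who delivered in a Kent hospital, or who joined one of the three studies, fits the description of the development cohort. She may also be counted in the validation cohort.

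To the extent that this happens, discrimination and calibration in that cohort move towards apparent performance, which is performance in the data used for fitting. Both would look better than they are and would be reported as external evidence. The models are meant for counselling women about pregnancy, so a calibration result that flatters the model matters in practice. Calling the validation sets international also hides the fact that most come from the development country.

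**Working it through.** **1. Count of datasets.** Inputs are the stated total of seven and the list of external sources.

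- 1 development + 1 Kent + 1 SCREAM + 1 Ontario + 3 obstetric studies = 7, which reproduces the stated figure.
- Counting Kent as two (West and East), the obstetric studies as one, or both, gives 8, 5 or 6. None of these matches.
- External datasets: 7 − 1 = 6. UK: 1 + 3 = 4. Outside the UK: 2.

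**2. Place, period and entry, set side by side.**

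| Dataset | Place | Period | Can it share pregnancies with development? |
|---|---|---|---|
| Development | UK-wide, diagnosed kidney disease | 1997 onwards | – |
| Kent | UK | not given | Yes on place; period unknown |
| Three obstetric studies | UK | 2010–2018 | Yes on place and period |
| SCREAM | Stockholm | not given | No basis in the text |
| Ontario | Canada | births 2007–2020 | No basis in the text |

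None of the exclusions in the eligibility paragraph concerns membership of another dataset.

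**3. Possible size.** The article gives neither the overlap nor the size of the development set, so this step is an illustration under assumed inputs.

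- Parameters: 17, counted from Table 1 with continuous predictors entered linearly. Age 1 + ethnicity (four groups) 3 + BMI 1 + parity 1 + hypertension 1 + aetiology (eight categories) 7 + eGFR 1 + proteinuria (three levels) 2 = 17.
- Assumed: independent standard normal predictors, 8 of the 17 with a log-odds ratio of 0.3 per SD, and intercept −1.6. The linear predictor then has SD √(8 × 0.3²) = 0.849, and averaging the logistic risk over that distribution gives a prevalence of about 20%.
- The full logistic model is fitted to N pregnancies. The validation set has 300, of which a share f is drawn from the development data and the rest are new. There are 300 replicates.
- Measures: the c-statistic of the linear predictor, and the slope from regressing the outcome on the linear predictor (1 is ideal).

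Mean c-statistic / calibration slope:

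| N | no overlap | 50% overlap | 100% overlap |
|---|---|---|---|
| 494 | 0.687 / 0.72 | 0.719 / 0.86 | 0.746 / 0.99 |
| 1000 | 0.699 / 0.85 | 0.716 / 0.94 | 0.733 / 1.02 |
| 3000 | 0.710 / 0.96 | 0.715 / 0.99 | 0.717 / 1.00 |

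Monte Carlo standard errors are about 0.002 for the c-statistic and at most 0.012 for the slope. From no overlap to full overlap, the c-statistic gains 0.746 − 0.687 = 0.059 at N = 494, 0.034 at 1000 and 0.007 at 3000.

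A second simulation used 494 pregnancies, 17 parameters, 20% prevalence, backward elimination at 0.10 and 120 replicates. It gave a c-statistic of 0.772 in the development data against 0.739 in new women, a gap of 0.033. The slope in new women was 0.85, against 1.00 by construction in the development data. The direction is the same and the size is of the same order.

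**The case against.** A reader might infer that the four UK datasets are simply nested inside the development cohort, so that every woman in them has been used twice. The article does not support that, for three reasons.

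- Entry to the development cohort needs a kidney disease diagnosis, whereas study eligibility rests on eGFR alone. A woman in the Kent laboratory data with a qualifying eGFR and no recorded diagnosis can be validated on without having been in development. The article does not say that the obstetric studies enrolled only women with diagnosed CKD.
- Kent's dates are not given, so a shared period cannot be asserted for it.
- Membership of the source cohort is not membership of the fitted model. Women without a preconception eGFR are excluded and listwise deletion is applied, so overlap among the pregnancies actually analysed may be smaller.

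It can also be said that 494 is a floor for a national dataset running from 1997, and that the optimism is slight if the true number is in the thousands. Results are to be evaluated cohort by cohort, so SCREAM and Ontario would stand on their own, and bootstrapping addresses overfitting separately. Finally, rules for removing duplicates may sit in a fuller protocol.

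All of this limits the extent and the likely size, and it stands. It does not remove the point. The silence on duplicates alone would not be a finding. The difficulty is in what the article does state: a development population without regional or end-date limits, and cohorts from the same country labelled external to it. For diagnosed women in the UK validation sets, those two statements do not fit together unless a separation is made.

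**Conclusion.** The point holds as a possible overlap of unstated extent. Four of six external datasets come from the country that the development cohort covers, three of them also from within its period, and nothing in the stated eligibility rules keeps the same pregnancy out of both. Only SCREAM and Ontario are clearly separate on the text given.

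The numerical consequence depends on two unknowns, the share of overlapping pregnancies and the size of the development set. Under the assumed inputs, optimism is material near 494: with full overlap up to about 0.06 on the c-statistic, and a true slope of 0.72 shown as about 1. It is slight at 3000. These figures should not be read as an estimate of bias in this study. The part that does not depend on them is the label: validation on pregnancies that helped fit the model is not external at any sample size. Because this touches the study's central validation claim, it should be settled before the models are fitted.

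**What to change.** Before fitting, remove from the development data the pregnancies delivered at the Kent hospitals over the period of the Kent data, for example by provider code. Where linkage allows, also remove those enrolled in the three UK studies; otherwise remove pregnancies at the recruiting units during the recruitment dates. Where neither is possible for a cohort, report it as potentially overlapping with development and rest the external-validation claim on SCREAM and Ontario. State the Kent dates and the rule used. If separation is already planned, one sentence saying so is enough.

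The cost is some loss of development pregnancies, in a number that the article does not allow to be sized. The loss is larger if whole recruiting units have to be left out. Identifiers for the study participants may not be available, in which case relabelling is the minimum change and costs only wording. After fitting, the same correction would mean refitting the models.

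### Outcome (i) counts renal replacement therapy only if it starts inside the 6-week to 12-month window, so therapy begun earlier and still continuing falls outside that limb

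*Protocol article*

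**What the plan says.** The article has no numbered sections, so places are named by content.

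- **Outcome paragraph (after Table 1).** "There are two binary outcome measures". The first is a fall of at least 25%, worded as "reduction in eGFR or initiation of renal replacement therapy between 6 weeks and 12 months postpartum".
- **Aim (opening paragraph).** The same window is attached to the therapy limb: "initiation of renal replacement therapy between 6 weeks and 12 months postpartum".
- **Reason for the window (outcome paragraph).** "serum creatinine levels may peak within the first few weeks postpartum but return to pre-pregnancy concentrations". No reason specific to renal replacement therapy is given.
- **Exclusions (eligibility paragraph).** The dialysis exclusion reads "Women established on dialysis at time of conception". Nothing excludes women who start later.
- **Missing data (sample size paragraph).** "Listwise deletion will be applied for model development", then "A sensitivity analysis will be performed using multiple imputation".
- **Closing statement of purpose.** The outcome is restated as "having a 25% or greater decline in kidney function or initiation of renal replacement therapy", with no window.

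**The concern.** The window suits one limb of the composite and not the other. Delaying the eGFR assessment until 6 weeks avoids counting a passing rise in creatinine as lasting loss of function. Therapy that begins at, say, 24 weeks' gestation or 3 weeks after birth and is still running at 6 weeks is not a passing rise, yet the start-date condition keeps it out of the therapy limb.

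These women have some of the most severe kidney outcomes in the cohort, and they plausibly concentrate at low pre-pregnancy eGFR. If they are not counted, predicted risk is too low where counselling depends on it most, and the eGFR gradient is likely to be flattened. Neither bootstrap validation nor external validation under the same definition would reveal this, because the fault lies in the outcome label and not in the fit.

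A second problem follows. Whether such a woman is counted through the eGFR limb depends on which laboratory values each dataset happens to hold. The same clinical course could be an event in one cohort and a non-event or a deleted record in another.

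**Working it through.** **No figure in the article tests this point.** The only sample size given is 494 pregnancies. Its inputs (outcome risk, expected model fit, number of parameters) are not stated, so it can be neither confirmed nor refuted. The point does not depend on it, and it is used below only as a scale.

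**Step 1: does the window govern the therapy limb?** The window phrase follows directly after the therapy limb. It either covers both limbs or covers the therapy limb alone. On both readings, a start before 6 weeks does not qualify.

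**Step 2: where does an early starter go?** She is eligible, because she was not on dialysis at conception. Three routes follow:

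| Situation in the window | Classification under the printed definition |
|---|---|
| Still on therapy, creatinine recorded, computed eGFR down by at least 25% | Event, through the eGFR limb |
| Still on therapy, creatinine recorded, computed fall under 25% | Non-event |
| Still on therapy, no eGFR recorded | Not stated; deleted if the outcome is treated as missing, or a non-event if no recorded event is read as none |

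The second row can occur. Creatinine on dialysis partly reflects clearance by the treatment. A woman who starts from a very low eGFR also has little room to fall: an assumed change from 12 to 10 ml/min/1.73 m² is (12 − 10)/12 = 17%.

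A woman who recovered and stopped therapy before 6 weeks is judged on her eGFR, which is reasonable.

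**Step 3: illustration in a low-eGFR group (all inputs assumed).** Let the true risk be 30 per 100, and let *u* per 100 be early starters still on therapy whom the eGFR limb does not capture.

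- Coded as non-events: recorded risk = (30 − *u*)/100.
- Deleted: recorded risk = (30 − *u*)/(100 − *u*).

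| *u* | Coded as non-events | Deleted |
|---|---|---|
| 0 (all captured) | 30% | 30% |
| 5 | 25% | 25/95 = 26.3% |
| 10 | 20% | 20/90 = 22.2% |
| 15 | 15% | 15/85 = 17.6% |

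The row *u* = 5 also describes 10 early starters per 100 of whom the eGFR limb captures half. At *u* = 10 the odds fall from 30/70 = 0.43 to 20/80 = 0.25 (a 42% reduction) or to 20/70 = 0.29 (a 33% reduction).

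**Step 4: illustration for a whole cohort of 494 (assumed).** With true risk of 10% to 30% there are 49 to 148 events. If 2% to 20% of these are uncaptured early starts, the loss runs from 49.4 × 0.02 = 1 event to 148.2 × 0.20 = 30 events. In the middle, at 20% risk with 10% of events lost, there are 98.8 events and 9.9 are lost. The recorded risk is 88.9/494 = 18.0% if they are coded as non-events, or 88.9/484.1 = 18.4% if deleted.

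**The case against.** The strongest reply has four parts.

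1. **The composite offers another route.** The two limbs are joined by an *or*, the eGFR is a formula value, and nothing bars a creatinine taken on dialysis. A reader might infer that all early starters are coded as non-events or deleted. The article does not say so, and some would count through the eGFR limb. Deletion needs the further step that no eGFR exists in the window and the outcome is then treated as missing. This part stands, and it limits the claim to women who *may* be missed. It does not remove the problem, since capture then rests on incidental laboratory values.

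2. **This is a short article, and coding rules usually sit in the full protocol.** That is true of a missing rule. Here a rule is printed: the window is attached to starting therapy in both the aim and the outcome paragraph, with a reason that does not fit it. A fuller document may handle these women, but the printed definition would still need correcting.

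3. **Multiple imputation is planned as a sensitivity analysis.** It does not change women classed as non-events. For deleted women, it would not necessarily remove a bias in which the outcome itself causes the missing value.

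4. **The size is assumed.** This stands in full. The article gives no number of early starters, and eligibility extends to any eGFR below 90, so they may be few. With small losses the overall risk barely moves.

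**Conclusion.** The point holds in a limited form. As printed, therapy started in pregnancy or in the first 6 weeks and still continuing does not meet the therapy limb of outcome (i). The stated reason for the window does not justify that, and the closing purpose is wider than the outcome to be modelled.

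The direction of bias is toward underestimated risk, most likely at low pre-pregnancy eGFR. This rests on two assumptions: that early starters concentrate there, and that the eGFR limb does not capture all of them. The size is unknown. The illustrations run from almost nothing (1 event in 494 pregnancies) to a halving of recorded risk in a low-eGFR group (30% to 15%), and none of their inputs comes from the article.

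A reader might conclude that the worst kidney outcomes are systematically removed and the model seriously miscalibrated. The article does not support that: it states no coding path for these women and no count of them. Because the point concerns the definition of a modelled outcome, it should be settled before any model is fitted.

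**What to change.** - Keep the 6-week start for the eGFR component only.
- Count as an event any renal replacement therapy begun after conception and up to 12 months postpartum that is ongoing at or after 6 weeks postpartum. Women who stopped before 6 weeks are then judged on eGFR. This is a rule for coding the outcome and has no bearing on treatment.
- Use the same definition, with its window, in the aim, the outcome paragraph and the closing statement of purpose.
- Apply it in every cohort whose data hold therapy dates, and report which cohorts do not.
- Report, by cohort, how many women started therapy before 6 weeks and how many the eGFR limb alone would have captured. That replaces the assumed figures above with real ones.

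**Cost.** A change of wording and some recoding of existing data; the development data are linked to the UK Renal Registry. The rule needs continuation or stop dates as well as start dates. The article does not show that every validation cohort holds them, so ascertainment may be incomplete in some, and their validation results should be read with that in mind.
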